### Blinding

Blinding of participants and intervention providers is not feasible due to the nature of behavioural interventions. However, outcome assessment is blinded wherever possible. Performance-based measures (eg, HGS, physical activity sensors, HRV) are conducted by study staff who are unaware of participants’ group allocation. Laboratory analyses are carried out externally without access to allocation data. For the qualitative interviews, complete blinding cannot be ensured, as participants may refer to their intervention experiences. To reduce potential bias, interviews are conducted by researchers not involved in intervention delivery, and participants are not actively asked to reveal their group allocation. These procedures are implemented to minimise detection bias and to safeguard the validity of outcome assessment.

### Sample size calculation

The study is powered to detect a minimal clinically relevant effect of 3.3 points on the CFQ.^61^ Based on an SD of 4.4 in a sample of patients with post-COVID-19 syndrome and fatigue diagnosed by CFQ,^62^ the estimated effect size is d=0.75. Assuming this effect, a two-tailed independent t-test with a significance level of α=0.05 requires a total of 78 participants to detect a group difference with a power of 90%. In order to avoid a possible loss of power due to a dropout rate of up to 20%,^63^ it is planned to include 100 participants in the study and assign them to the two study groups in a 1:1 ratio. Sample size calculation was performed using the ‘pwr’ package in R V.4.3.1.^64^

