### Interventions 

**Yoga**

The content of the yoga treatment was developed on the basis of systematic literature research on previous yoga interventions, particularly for patients with cancer and patients with ME/CFS, as well as the experience of an interdisciplinary team with several years of experience in yoga therapy, integrative medicine and clinical practice. The yoga treatment is carried out by certified and experienced yoga teachers once a week in consistent groups of a maximum of 11 participants on site and covers a total period of 12 weeks. All yoga instructors hold a minimum 500 hours yoga teacher certification from a recognised yoga alliance and have additional experience in yoga therapy or clinical applications. Prior to the start of the trial, instructors participated in a standardised preparatory training conducted by the study team, covering post-COVID-19 symptomatology, PEM and pacing, as well as the study-specific manual. Adherence to the intervention manual is supported by the detailed written curricula, standardised video material and two supervision meetings (one during and one after the intervention) with the study centre.

The intervention includes the three main yogic elements: yoga postures (āsāna), breathing techniques (prānāyāma) and meditation (dhyāna). It lays an emphasis on postures and breathing techniques considered effective for fatigue with a focus on laying positions (as in isometric yoga), seated poses (practised on a chair), side bends, passive inversion postures and backbends (ie, supported spinal extensions) as well as targeted breathing exercises to strengthen the respiratory muscles and increase the lung volume by mobilising the diaphragm.

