### Health education

Health education is an established therapy for the treatment of cancer-related fatigue, for example, in patients with breast cancer, and is delivered by experienced therapists.^66^ The health education courses are held once a week for 90 min over 12 weeks on site by healthcare professionals. All educators are experienced clinicians (eg, physicians, physician assistants, physiotherapists, nurses) and received a structured briefing on post-COVID-19 symptomatology, PEM and pacing as well as a detailed teaching manual before study initiation. The courses are didactic in nature and consist of lectures on topics of interest to patients with post-COVID-19 syndrome and fatigue, followed by questions and discussion sessions. The 12-week programme contains the following topics: (1) introduction, behaviour change and balance of health; (2) post-COVID-19 syndrome, fatigue and ME/CFS; (3) autonomic nerve system, relaxation and stress management; (4) movement and pacing with post-COVID-19 syndrome; (5) sleep and sleep hygiene; (6) internal communication and cognitive restructuring; (7) external communication; (8) nutrition with fatigue; (9) dealing with symptoms of anxiety, depression and post-traumatic stress syndrome; (10) social network; (11) everyday strategies and resilience and (12) review and relapse prevention. Each session starts with a 15 min group check-in time, where patients can share their weekly experiences and in-between lecture sections patients are engaged in group work or reflection practices. To ensure fidelity, all sessions follow a standardised manual and presentation slides, supplemented by two supervision meetings (one during and one after the intervention) with the study centre. The health education group, like the yoga group, will only meet once a week for 90 min. In addition, the aim is to consolidate and apply what has been learnt for 60 min per week at home. For this purpose, the participants receive the course material and eight health education videos (duration 7:54–14:04 min) specifically developed for patients with post-COVID-19 syndrome through an online platform.

Participants received no financial compensation. All participants may continue their routine care as prescribed, for example, by their general practitioner. Adherence to the interventions will be assessed.

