### Statistical analysis

All analyses are based on the intention-to-treat population, that is, all participants included in the study are analysed in the group to which they were originally assigned, regardless of the treatment they actually received. Missing values are handled using multiple imputation. The multiple imputation procedure will be conducted using R (V.4.3.1), employing the ‘missForest’ package for handling missing data.^91^ The multiple imputation procedure using the ‘missForest’ package involves handling missing values by employing a non-parametric approach. This package uses a Random Forest algorithm to predict missing values based on the observed data, accommodating both numerical and categorical variables. Through iterative variable iterations, missing values are imputed by leveraging predictions from the remaining variables within the dataset. In addition, a per-protocol analysis is conducted as a sensitivity analysis. The per-protocol population is defined as all participants who provide data at the respective time point and participate in at least 8 of the 12 intervention appointments.

The primary outcome measure is analysed confirmatory using a univariate analysis of covariance, in which the primary outcome measure is modelled as a function of group allocation (fixed factor), study centre (binary covariate), treatment credibility and expectation (linear covariates) and the respective baseline values (linear covariate). Within this model, the adjusted group difference and its 95% CI are estimated and tested for superiority of the intervention over the control group using a two-sided t-test at the α=0.05 level. The secondary end points are analysed exploratively (without correction for multiple testing) using the same models as the primary end point. To estimate the clinical significance of the results, change scores and effect sizes (Hedges’ g) are calculated for between-group comparisons.

HRV parameters within groups will be compared at two different time points using a Wilcoxon signed rank test. The results will be presented as medians and IQRs, Hodges-Lehmann estimator (HLE) of the differences, 95% CI and effect sizes r. A comparison between groups will be undertaken by examining the HLE, the 95% CI and the effect sizes r simultaneously.

All analyses will be conducted using R V.4.3.1, with the ‘psych’‘ package used for psychometric assessments.^92^

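### Both treatments are delivered in groups, but neither the sample size nor the primary ANCOVA allows for correlation within course groups, so the confidence interval is too narrow and the test too liberal if course groups differ

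*Protocol article*

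**What the plan says.** **Sample size (Sample size calculation).** The trial is planned on "a two-tailed independent t-test with a significance level of α=0.05". The inputs are a difference of 3.3 points on the Chalder Fatigue Scale (CFQ) and an SD of 4.4. From these, "the estimated effect size is d=0.75", which "requires a total of 78 participants to detect a group difference with a power of 90" per cent. The 78 is raised to 100 for up to 20% dropout. No ICC or design effect appears.

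**Delivery (Interventions).** Yoga is taught "once a week in consistent groups of a maximum of 11 participants on site" for 12 weeks. For the comparator, "The health education group, like the yoga group, will only meet once a week for 90 min". The Health education section gives no group size and does not say that membership is fixed. In both arms each session opens with a 15-minute check-in at which members share their week, and health education adds group work. The Discussion names social support and group interaction among the non-specific effects that the comparator is meant to match.

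**Analysis (Statistical analysis).** In the confirmatory model "the primary outcome measure is modelled as a function of group allocation (fixed factor"), study centre, treatment credibility and expectation, and baseline. The 95% CI and the two-sided t-test come from this model, and the secondary endpoints use the same one. There is no term for course group. Randomisation is by individual, stratified by gender and centre.

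**The concern.** People who spend 12 weeks in the same course share a setting, a timetable and each other's company. Their self-reported fatigue at week 12 can therefore be more alike than that of people in different courses. Each course delivers only one of the two treatments, so differences between courses do not cancel when the arms are compared; they add to the variance of the treatment effect.

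A model without a course term counts that extra variance as if it averaged out over all participants. Its standard error is then too small, and a run of good or poor courses in one arm can pass for a treatment effect. This affects the one confirmatory test, and the secondary endpoints that share its model.

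Study centre in the model does not solve this. A centre effect common to both arms is removed, but variation between courses within a centre and arm is not.

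**Working it through.** **1. The plan's own figure.** d = 3.3/4.4 = 0.75. The non-central t calculation needs 38.35 per arm, so 39 per arm, 78 in total, with power 90.5%. Dropout: 78/0.80 = 97.5, so 98, rounded up to 100. The figure reproduces, on the assumption of independent participants.

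**2. Inputs for clustering.** None of these is stated except the yoga maximum of 11.
- ICC: assumed 0.01 to 0.10, taken within centre and arm.
- Analysed participants per course group, m: 6.5, 8.8 or 11.
  - 6.5: 50 per arm needs at least five groups of 11; I assume six over three centres, so 39/6 = 6.5.
  - 8.8: a full yoga group less 20% dropout, 11 × 0.80.
  - 11: a full yoga group with no loss.
- Both arms are taken as clustered at first.

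**3. Formulas.**
- Design effect: DE = 1 + (m − 1) × ICC.
- Correct CI width relative to the planned width: √DE.
- Actual error rate of the nominal 5% test: 2 × [1 − Φ(1.96/√DE)].
- Power: non-central t with 76 df and non-centrality 0.75 × √(39 / (2 × DE × (1 − r²))), where r is the correlation of baseline with outcome. This takes the covariate gain as a proportionate cut in total variance.

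**4. Example, ICC 0.05.** With m = 6.5, DE = 1 + 5.5 × 0.05 = 1.275 and √DE = 1.129. With m = 11, DE = 1 + 10 × 0.05 = 1.50 and √DE = 1.225.

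**5. Results, both arms clustered, 39 analysed per arm.**

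| ICC | m | DE | CI wider by | Error rate | Power, r = 0 | Power, r = 0.5 |
|---|---|---|---|---|---|---|
| 0 | – | 1.00 | 0% | 5.0% | 90.5% | 96.5% |
| 0.01 | 6.5 | 1.06 | 3% | 5.6% | 88.9% | 95.7% |
| 0.01 | 11 | 1.10 | 5% | 6.2% | 87.7% | 94.9% |
| 0.05 | 6.5 | 1.28 | 13% | 8.3% | 82.5% | 91.7% |
| 0.05 | 8.8 | 1.39 | 18% | 9.6% | 79.2% | 89.3% |
| 0.05 | 11 | 1.50 | 22% | 11.0% | 76.1% | 86.9% |
| 0.10 | 6.5 | 1.55 | 24% | 11.5% | 74.7% | 85.8% |
| 0.10 | 11 | 2.00 | 41% | 16.6% | 63.8% | 76.1% |

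**6. Only yoga clustered.** The variance factor is (1 + DE)/2. At ICC 0.05 it is (1 + 1.275)/2 = 1.14 to (1 + 1.50)/2 = 1.25. The interval is then 7% to 12% wider, the error rate 6.6% to 8.0%, and power at r = 0 is 86.6% to 83.3%.

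**7. What baseline adjustment can and cannot do.** At r = 0.5 (assumed) the variance is multiplied by 0.75, which balances a DE of 1/0.75 = 1.33. Power then returns to 90.5%. The ratio of the correct to the planned standard error stays √DE, because adjustment shrinks both alike.

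**The case against.** The case on the other side has weight.

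- **Delivery is standardised.** Both arms use manuals, standard materials and two supervision meetings, which limit variation between courses. They do not show that it is nil.
- **The ICC is unknown and may be small.** At 0.01 the interval is only 3% to 5% too narrow and the error rate about 6%. This stands, and it is why the size is a range.
- **A random effect from few groups is imprecise** and may be estimated at zero, so one could keep it as a sensitivity analysis. That is partly a matter of choice. But the protocol fixes the confirmatory model term by term, and as written it assumes exactly zero correlation.
- **Recruitment was due to finish by September 2025**, so restating power cannot change the design. True; the analysis can still change.

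Four stronger readings are tempting, and the documents do not support them:
- *Both arms run in fixed groups of up to 11.* This is stated for yoga only. The comparison drawn in the Health education section concerns meeting once a week for 90 minutes.
- *Each group keeps the same instructor.* Neither intervention section says so, and different professionals could teach the education topics.
- *The 90% power is not delivered.* No ICC is given, and the planned test is a baseline-adjusted ANCOVA. At r = 0.5 and m = 6.5 power is still about 92% at ICC 0.05.
- *Power collapses on group-level degrees of freedom.* With about 12 groups and 10 df, power is 84.7% even at ICC 0, so most of that loss at small ICCs is a penalty for few groups. Satterthwaite degrees of freedom would normally exceed 10 when the group variance is near zero.

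**Conclusion.** The point holds for the interval and the test. Any positive correlation within course groups makes the planned 95% CI too narrow and the confirmatory test anti-conservative, and neither centre nor baseline in the model corrects that. Under the assumptions above, with both arms clustered, the correct interval is about 3% to 41% wider and the error rate about 6% to 17%. At ICC 0.05 these are 13% to 22% and 8% to 11%. The inflation is smaller if only yoga is clustered.

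On power the point is conditional. The 78 is right under independence. Without covariate gain, power at ICC 0.05 is about 76% to 83%; with r = 0.5 it is about 87% to 92%, all at 76 df. So 90% holds only if the ICC is near zero or covariate gain makes up the loss. The ICC, the group sizes analysed and r are my assumptions.

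**What to change.** Before the data are analysed:
1. Keep the course-group identifier for every participant in the analysis file.
2. Fit the primary model, and the secondary models that copy it, with a random intercept for course group and Satterthwaite or Kenward-Roger degrees of freedom. If the health education groups were not stable, use a partially nested model with the random effect in the yoga arm only.
3. Report the estimated ICC with its uncertainty.
4. State that the 90% power assumes no clustering, and give a range over plausible ICCs.
5. Describe the size and stability of the health education groups.

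Keep N at 100. The cost is a change of analysis wording, one identifier that course lists should already hold, somewhat wider intervals, fewer degrees of freedom, and an ICC that will be imprecise with so few groups. The change should be dated before results are seen; made afterwards, the model would no longer be confirmatory.

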### Interventions 

**Yoga**

The content of the yoga treatment was developed on the basis of systematic literature research on previous yoga interventions, particularly for patients with cancer and patients with ME/CFS, as well as the experience of an interdisciplinary team with several years of experience in yoga therapy, integrative medicine and clinical practice. The yoga treatment is carried out by certified and experienced yoga teachers once a week in consistent groups of a maximum of 11 participants on site and covers a total period of 12 weeks. All yoga instructors hold a minimum 500 hours yoga teacher certification from a recognised yoga alliance and have additional experience in yoga therapy or clinical applications. Prior to the start of the trial, instructors participated in a standardised preparatory training conducted by the study team, covering post-COVID-19 symptomatology, PEM and pacing, as well as the study-specific manual. Adherence to the intervention manual is supported by the detailed written curricula, standardised video material and two supervision meetings (one during and one after the intervention) with the study centre.

The intervention includes the three main yogic elements: yoga postures (āsāna), breathing techniques (prānāyāma) and meditation (dhyāna). It lays an emphasis on postures and breathing techniques considered effective for fatigue with a focus on laying positions (as in isometric yoga), seated poses (practised on a chair), side bends, passive inversion postures and backbends (ie, supported spinal extensions) as well as targeted breathing exercises to strengthen the respiratory muscles and increase the lung volume by mobilising the diaphragm.

The intervention duration of 150 min per week is based on previous studies on yoga interventions specifically for fatigue patients and on recommendations such as those of WHO, which recommend at least 150 min of moderate-intensity aerobic physical activity per week spread over at least 3 days per week for adults, including people with chronic illnesses.^65^ The German guideline on long covid/post-COVID-19 recommends a training duration of 40–60 min, 3–6 times per week.^7^ However, previous experience with this patient population suggested that it is difficult for patients to travel to the study site several times a week to attend yoga classes, while regular attendance is of great importance for the success of the treatment.^37 54^ It was therefore decided that the group would only meet once a week on site, for a total duration of 90 min including a maximum of 40–60 min of āsāna (posture) practice. Each session starts with a 15 min group check-in time, where participants can share their weekly experiences, followed by 5–15 min of meditation (including Om-sounding) and bhāvana (setting an intention for the class) and a 5–10 min breathing exercise. Each session is concluded by 9–10 min of rest in shavāsāna and 4 min group closing. To conclude the total physical activity time of 150 min a week, participants have access to yoga videos specially developed for the study and based on the on-site programme. The online material consists of 19 yoga videos of varying length and intensity (duration 0:48 to 47:04 min) and is sectioned by ‘energy level’ needed to practise them. This ensures that participants receive the recommended amount of yoga, but that the yoga practice can be better integrated into everyday life, thereby promoting compliance. Participants are encouraged to engage in pacing-orientated, home-based yoga practice for approximately 60 min per week. The duration of home practice will be recorded through self-reported weekly practice times.

### Health education

Health education is an established therapy for the treatment of cancer-related fatigue, for example, in patients with breast cancer, and is delivered by experienced therapists.^66^ The health education courses are held once a week for 90 min over 12 weeks on site by healthcare professionals. All educators are experienced clinicians (eg, physicians, physician assistants, physiotherapists, nurses) and received a structured briefing on post-COVID-19 symptomatology, PEM and pacing as well as a detailed teaching manual before study initiation. The courses are didactic in nature and consist of lectures on topics of interest to patients with post-COVID-19 syndrome and fatigue, followed by questions and discussion sessions. The 12-week programme contains the following topics: (1) introduction, behaviour change and balance of health; (2) post-COVID-19 syndrome, fatigue and ME/CFS; (3) autonomic nerve system, relaxation and stress management; (4) movement and pacing with post-COVID-19 syndrome; (5) sleep and sleep hygiene; (6) internal communication and cognitive restructuring; (7) external communication; (8) nutrition with fatigue; (9) dealing with symptoms of anxiety, depression and post-traumatic stress syndrome; (10) social network; (11) everyday strategies and resilience and (12) review and relapse prevention. Each session starts with a 15 min group check-in time, where patients can share their weekly experiences and in-between lecture sections patients are engaged in group work or reflection practices. To ensure fidelity, all sessions follow a standardised manual and presentation slides, supplemented by two supervision meetings (one during and one after the intervention) with the study centre. The health education group, like the yoga group, will only meet once a week for 90 min. In addition, the aim is to consolidate and apply what has been learnt for 60 min per week at home. For this purpose, the participants receive the course material and eight health education videos (duration 7:54–14:04 min) specifically developed for patients with post-COVID-19 syndrome through an online platform.

Participants received no financial compensation. All participants may continue their routine care as prescribed, for example, by their general practitioner. Adherence to the interventions will be assessed.

## Outcome measures

### Primary outcome measures

#### Fatigue

In its standard version (range 0–33), the CFQ is used to assess the severity of fatigue within the last 4 weeks. It comprises 11 items in a 5-point Likert scale format (0–4 points), seven of which relate to the extent of physical exhaustion and four to the extent of mental exhaustion. In its binomial evaluation (range 0–11), it can be used to categorise patients with and without fatigue with a cut-off of ≥4 indicating fatigue.^65 67^ The CFQ demonstrates strong internal consistency with split-half reliabilities of 0.85 and Cronbach’s α values ranging from 0.86 to 0.92.^68^

### Secondary outcome measure

#### Postexertional malaise

The DSQ is a standardised instrument for ME/CFS diagnosis.^69 70^ Its validated PEM subscale has been used since 2020 to assess PEM frequency and PEM severity in patients with post-COVID-19 syndrome.^22 71^ The PEM subscale comprises five items on frequency, five on severity and five on duration and classification.^71^

#### Health-related quality of life

The SF-12 is the most commonly used instrument in clinical studies to measure generic health-related quality of life. The SF-12, a validated 12-item short form of the SF, shows no significant difference to its longer versions in the assessment of the physical and mental component score. For this reason, the SF-12 is used to reduce the burden on fatigue patients when completing the questionnaires.^72^,^74^

